**Figure 1 F1:**
[figure not shown]
Trial design.

### Study settings and participants

This study will be conducted in long-term care homes for older people who suffer from physical and/or mental disabilities with deficiencies in coping with daily life.

#### *Inclusion criteria for long-term care homes*

The long-term care homes, funded by the government, must be under the Social and Welfare Department of Hong Kong (HK) and thus meet a set of standard criteria as set by the HK Government. The staffing pattern, staff-resident ratio, bed space, the other service criteria of the facilities, and the nature of the residents are therefore similar in that they have to meet government standards. Additionally, the total number of residents must be 100 or above so as to maximize the chance of recruiting a sufficient number of participants in each care home (that is 15 to 16 - please refer to sample size for details).

#### *Exclusion criteria for long-term care homes*

Private nursing homes will be excluded due to the variations in their staffing pattern, the staff-resident ratio, bed space, the other service criteria of the facilities, and the nature of the residents.

The target population of this study is long-term care residents with dementia, communication impairment, and pain problems.

#### *Inclusion criteria for participants*

Participants must be ≥65 years old, of either gender. They must have been living in the long-term care home for >6 months to avoid anxiety and distress due to the unfamiliar new environment. Their general health must be stable (with no acute physiological or psychiatric illnesses, and no history of fractures or emergency hospital admissions within the past 3 months). Participants must be officially diagnosed with some form of dementia according to the DSM-IV criteria for dementia. Their cognitive state will be assessed by the Cantonese-Mini Mental State Examination (C-MMSE) [20]. The participants must have at least one pain-related diagnosis such as osteoarthritis, low back pain, or rheumatoid arthritis. Each participant’s communication ability will be assessed by the communication score based on two items in the Hong Kong version of the interRAI-Home Care (HC) Assessment (formerly called the Minimum Data Set-HC): (1) making one’s self understood; and (2) ability to understand others. These two items are rated on a 5-point scale: 0 = understood, 1 = usually understood, 2 = often understood, 3 = sometimes understood, 4 = rarely or never understood. A total communication score is summed from these two items and ranges from 0 to 8, with 0 meaning no communication problems and 8 meaning very severe communication impairment. Participants must have a communication score ≥5 to be eligible for recruitment into this study [21].

#### *Exclusion criteria for participants*

Exclusion criteria includes residents with: (1) a current medical condition and the need to be frequently admitted to hospital during the study period (for example, acute exacerbation of chronic obstructive pulmonary disease or renal failure, and so on); (2) co-morbid psychiatric disorders (for example, psychosis); or (3) a recent experience of distressing social circumstances (for example, the death of a close relative or friend within the previous 6 months) that may cause altered behavior patterns; and (4) terminal illness (for example, advanced cancer) and deemed not to have more than 6 months to live.

Although many kinds of chronic diseases such as diabetes mellitus and ischemic diseases may affect the pain sensation of older people, it is not uncommon for them to have multiple health problems. Residents who match all the inclusion criteria but have other kinds of chronic illnesses will still be recruited, providing the illnesses are not acute. Each participant’s medical history will be recorded in detail.

#### *Sample size*

We will randomly select eight long-term care homes that agree to join this study. As no similar cluster-randomized trial has been reported in the literature, we can only estimate the intracluster coefficient with a range between 0 and 0.1 [22]. The intensity of pain can vary according to the different natures and sources of the pain. As this study is not limited to participants suffering from a particular type of pain, we anticipate that variations in the nature of participants’ pain will be considerable. Due to its heterogeneous nature, we assumed an intracluster correlation of 0.02. The pilot study was able to detect a mean difference of 13.41 points on the MSQ score (95% confidence interval 8.923 to 17.897) and -0.3 points on the C-PAINAD (95% confidence interval -4.459 to 0.169) between the pre- and post-tests [18]. After averaging the effect sizes calculated based on these two mean differences, this was equivalent to an effect size of 0.65. In order to secure an appropriate effect size, a more conservative approach of using an effect size of 0.4 was used to calculate the sample size. With a significance level (α) of 0.05 and power (1-β) 0.8 for a two-sided test, the sample size calculation gives about 38 participants for each group in order to evaluate a mean difference in MSQ and C-PAINAD scores between the experimental and control groups. Accounting for the intracluster correlation, a variance inflation factor of 1.31 will be multiplied to this calculated sample size. Further accounting for a 15% drop-out rate over the period based on two similar studies [13,18], a total number of 61 participants per group is required, resulting in a total proposed sample size of 122. This means we will recruit 15 to 16 participants in each long-term care home.

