The Protocol was used to guide the pain management of 30 care home residents with dementia, with at least one pain-related diagnosis, for 8 weeks. Before the implementation, only five residents had been prescribed pain medications. Pain medications administered to the residents were quantified by the Medication Quantification Scale (MQS) [19]. During the study period, the mean MQS score increased from 10 (SD 14.23) at week 1 to 23.41 (SD 10.58) at week 8. The percentage of residents given pain medications increased to 23.33% (n = 7) at week 8. Similarly, only six residents were receiving non-pharmacological interventions at week 1. Towards the end of the study period, 17 residents were receiving non-pharmacological pain-relieving interventions such as hot pads, ice therapy, and massage. The mean pain score of the 30 residents decreased slightly from 2.87 (SD 1.30) at week 1 to 2.57 (SD 1.32) at week 8. Although this study did not show a statistically significant reduction of pain scores, probably due to the small sample size, it did show clinical relevance in improving pain management. Incorporation of this Protocol into the long-term care home’s daily routine encouraged well-organized pain recording for each resident, allowing further comparisons of pain treatment effectiveness. Besides this pilot study, no other study has been conducted to evaluate the effectiveness of similar protocols in improving pain management practice.

The aim of this study is to investigate the extent to which the implementation of the Observational Pain Management Protocol can improve the management of pain for older care home residents with dementia. Based on the findings in our pilot study [18], we hypothesize that the implementation of the Protocol will result in an improvement in pain management for residents with dementia, as manifested in an increased use of both pharmacological and non-pharmacological pain treatments. As a consequence, behavioral pain scores will be lower due to better pain management. The following two research objectives have been derived:

1. To investigate whether a systematic use of the Protocol improves pain management, as manifested by the increased use of pharmacological and non-pharmacological pain treatments for residents with dementia.

2. To investigate whether the use of this Protocol results in lower observational pain scores for residents with dementia.

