#### *Chinese - Pain Assessment IN Advanced Dementia (C-PAINAD)*

The C-PAINAD consists of five pain behaviors: breathing, negative vocalization, facial expressions, body language, and consolability. Each behavior is rated from 0 to 2 according to the severity of behavior exhibited, thus giving a total score of 0 to 10. Construct validity was supported by the C-PAINAD’s ability to differentiate pain from other pain-free conditions. It can detect pain among people with dementia. Exploratory factor analysis was used to evaluate the construct validity in which one major factor (that is, pain) was extracted and the percentage of variance was 51.2% [40]. The correlation coefficient was 0.68 when comparing the C-PAINAD with the Pain Visual Analog Scale. Generally, the findings were similar to those of the initial study validating the original PAINAD [28]. The results showed that the C-PAINAD was a simple, reliable, and effective pain assessment tool for cognitively impaired older people. A well-trained independent pain observer (that is, another research assistant who will not be involved in collecting data related to pain treatments) will use the C-PAINAD to observe participants’ pain scores weekly during the 4-week baseline assessment period. This will then continue weekly for 12 weeks during the Protocol implementation. Nurses in the experimental condition will also use the C-PAINAD to observe the pain-related behavior of participants daily for the 12 weeks of Protocol implementation. Pain scores collected by nurses will be compared to those collected by independent pain observers.

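### The pilot C-PAINAD interval in the sample-size section is impossible, the pilot did not detect a pain reduction, and the 80% power claimed for C-PAINAD is not delivered at the stated effect of 0.4

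*Protocol article*

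**What the plan says.** The Background describes the pilot: "The Protocol was used to guide the pain management of 30 care home residents with dementia". For medication, "the mean MQS score increased from 10 (SD 14.23) at week 1 to 23.41 (SD 10.58) at week 8". The mean pain score "decreased slightly from 2.87 (SD 1.30) at week 1 to 2.57 (SD 1.32) at week 8", and the authors add that "this study did not show a statistically significant reduction of pain scores".

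The Sample size section says the pilot could detect two pre-post differences: a "mean difference of 13.41 points on the MSQ score (95% confidence interval 8.923 to 17.897") and a change of minus "0.3 points on the C-PAINAD (95% confidence interval -4.459 to 0.169) between the pre- and post-tests". It continues: "After averaging the effect sizes calculated based on these two mean differences, this was equivalent to an effect size of 0.65". It then says that a more conservative 0.4 was used. With two-sided alpha 0.05 and power 0.8, it reports about 38 participants per group for comparing both MQS and C-PAINAD between arms. A variance inflation factor of 1.31 and 15% drop-out bring this to 61 per group, 122 in total.

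**The concern.** A confidence interval for a mean change should be centred on the estimate. This one extends 4.159 points below -0.3 and 0.469 above it. As printed, it tells the reader that a fall of almost 4.5 points is compatible with the pilot, on a scale where the pilot mean was below 3.

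The wording also credits the pilot with detecting a pain reduction that the Background says was not significant.

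Both problems concern the evidence given for the pain outcome, which is the trial's second research objective and one of the two outcomes on which the trial is sized. It therefore has to be checked whether the 80% power claimed for C-PAINAD follows from the figures given.

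**Working it through.** **Inputs.** From the Background: n = 30; C-PAINAD SDs 1.30 and 1.32; MQS SDs 14.23 and 10.58. From Sample size: mean changes -0.3 and 13.41, both printed intervals, effect sizes 0.65 and 0.4, 38 per group, factor 1.31, drop-out 15%, 61 per group.

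**1. Reproduce the MQS interval.**
- Pooled SD = √((14.23² + 10.58²)/2) = 12.539.
- 13.41 ± 1.96 × 12.539/√30 = 13.41 ± 4.487 = 8.923 to 17.897, exactly as printed.

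**2. Apply the same formula to C-PAINAD.**
- Pooled SD = √((1.30² + 1.32²)/2) = 1.310.
- -0.3 ± 1.96 × 1.310/√30 = -0.3 ± 0.469 = -0.769 to 0.169.
- The upper limit matches the printed one to three decimals; the lower does not. The printed midpoint is (-4.459 + 0.169)/2 = -2.145.

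**3. Could another method give -4.459?**
- The SD of change is largest at a pre-post correlation of -1: 1.30 + 1.32 = 2.62. The paired t-interval (29 df, t = 2.045) then reaches -0.3 - 2.045 × 2.62/√30 = -1.28. No paired t-interval from these SDs goes lower.
- A limit of -4.459 would need a change SD of 4.159 × √30/2.045 = 11.1. The items are rated "thus giving a total score of 0 to 10", so changes lie between -10 and 10 and their SD cannot exceed about 10 × √(30/29) = 10.2.

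**4. What the formula assumes.** It uses the pooled SD of the scores as the SD of change, √(SD₁² + SD₂² - 2ρSD₁SD₂). The two agree only when the correlation ρ is about 0.5. The article does not give ρ, so it is an assumption here. Paired t-intervals for C-PAINAD:

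| ρ | Lower limit | Upper limit |
|---|---|---|
| 0 | -0.99 | 0.39 |
| 0.3 | -0.88 | 0.28 |
| 0.5 | -0.79 | 0.19 |
| 0.7 | -0.68 | 0.08 |

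All four include 0.

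**5. Reproduce the 0.65.** C-PAINAD: 0.3/1.310 = 0.229. MQS: 13.41/12.539 = 1.070. Average = 0.649, as printed. Only means and SDs are used; the interval plays no part.

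**6. Reproduce the 38.** n per group = 2 × (1.96 + 0.8416)²/d².
- d = 0.4: 98.1, so 99.
- d = 0.65: 37.2, so 38, as printed.
- A one-sided test at 0.4 gives 78 and a paired design 49; neither is 38.
- Inflation: 38 × 1.31/0.85 = 58.6, so 59. Starting from 39 (the t-based 38.1 rounded up) it is 60.1, so 61. Either way the chain starts from 0.65.

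**7. Power for C-PAINAD.** Two-sample comparison, two-sided 0.05, normal approximation. The second column uses the effective size after drop-out and clustering, 61 × 0.85/1.31 = 39.6.

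| Effect (SD units; points = × 1.31) | 38 per group | 39.6 per group |
|---|---|---|
| 0.23 (0.30), pilot estimate | 17% | 17% |
| 0.40 (0.52), stated planning effect | 41% | 43% |
| 0.59 (0.77), lower limit by the authors' formula | 73% | 74% |
| 0.65 (0.85), averaged effect | 81% | 82% |

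Using the t distribution lowers these by about one point or less (at 38 per group, 71% at 0.59).

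**The case against.** The strongest reply is that the wrong limit feeds nothing. The effect size comes from the mean differences, 0.65 reproduces from correct inputs, and correcting the limit changes no sample size. That stands: taken alone, the limit is close to a clerical slip. A reader might infer that the misprint inflated the planning effect or produced the 38; step 5 shows that it did not.

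A reader might also infer that the corrected interval rules out the planning effect. The article does not support that. The effect it names, 0.4 (0.52 points), lies inside -0.769 to 0.169. The averaged 0.65 (0.85 points) falls outside that interval, but by only about 0.08 points. With a paired t-interval it is excluded only if the pre-post correlation exceeds about 0.37, which the article does not give. For the same reason, it would be wrong to write as fact that the pilot allows a fall of at most about 0.8 points.

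The power figures describe the simple comparison behind the sample-size calculation. The article also plans mixed-effects modelling of weekly measurements, whose power could differ and is not described by these figures. This limits what they say about the final analysis. It does not rescue the stated derivation, which claims 80% from 38 per group.

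Finally, the Background openly reports the non-significant pain result, so the claim of detection is loose wording rather than concealment. The two sections still disagree.

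**Conclusion.** Three things hold.

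- The printed C-PAINAD lower limit is impossible whatever the pre-post correlation. The authors' own formula gives -0.769.
- The pilot did not detect a C-PAINAD reduction. The interval includes 0, as printed and as corrected, and the Background says the reduction was not significant.
- The 80% power claimed for C-PAINAD does not follow. The 38 per group comes from 0.65, an average driven by MQS (1.07 against 0.23), not from the stated 0.4, which needs about 99. Power for C-PAINAD in the simple comparison is about 41 to 43% at 0.4, 17% at the pilot estimate, and 71 to 74% at the lower limit from the authors' formula.

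The power figures assume a C-PAINAD SD of 1.31 for conversion to points, the article's own inflation factor and drop-out, and a two-sample test. The first two conclusions need no assumption beyond the pilot means, SDs and sample size. The third matters most to a reader of the trial, because it concerns what a null result on pain would mean.

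**What to change.** In the Sample size section:

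- Recompute both pilot intervals, MQS and C-PAINAD, from the SD of within-resident change in the pilot data, and replace the printed ones.
- For C-PAINAD, replace the claim of detection with a statement that the pilot showed no significant reduction, in line with the Background.
- State which effect size produced 38 per group. Give the trial's power for C-PAINAD separately from MQS, at 0.4 and at the pilot C-PAINAD effect of 0.23. If the mixed model is expected to do better, give its power with the assumptions used.

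The cost is a short recalculation from pilot data already held and a few rewritten sentences. These corrections require no change in recruitment. The price is a less favourable stated power for the pain outcome.

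### The 61 per group rests on an effect size averaged over two different outcomes, not on the stated 0.4; C-PAINAD lacks the claimed 80% power at its own pilot effect, and the MQS pilot figures cannot cover all 30 residents.

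*Protocol article*

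**What the plan says.** The Sample size section takes two pilot changes, 13.41 points on the MQS (interval 8.923 to 17.897) and a fall of "0.3 points on the C-PAINAD (95% confidence interval -4.459 to 0.169"), and combines them: "After averaging the effect sizes calculated based on these two mean differences, this was equivalent to an effect size of 0.65". It continues that "a more conservative approach of using an effect size of 0.4 was used to calculate the sample size". For two-sided testing at alpha 0.05 and a target power of 80%, the result reported is that "the sample size calculation gives about 38 participants for each group". This one number is meant to serve the comparison of both MQS and C-PAINAD. Multiplying by 1.31 for clustering and allowing for 15% drop-out leads to 61 per group, 122 in total.

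The pilot figures are in the Background. For the MQS, "the mean MQS score increased from 10 (SD 14.23) at week 1 to 23.41 (SD 10.58) at week 8". Five of the 30 residents had been prescribed analgesics beforehand, and "The percentage of residents given pain medications increased to 23.33% (n = 7) at week 8". C-PAINAD went from 2.87 (SD 1.30) to 2.57 (SD 1.32), with the comment "Although this study did not show a statistically significant reduction of pain scores".

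The Outcome measures section lists MQS III, non-pharmacological treatments and C-PAINAD side by side. None is called primary.

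**The concern.** A standardized effect belongs to one outcome. The mean of a large effect on medication use and a small one on observed pain is the effect of nothing the trial will test, so 80% power at that value says nothing about either comparison. The stated retreat to 0.4 would soften this if it had been carried through, but 38 per group looks too small for 0.4.

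The MQS half of the average is also doubtful. Most pilot residents received no analgesic, and a scale that scores administered medication should then be zero for most of them. The printed SDs look too small for that.

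At stake is Objective 2, lower pain scores. If its power is far below 80%, a null C-PAINAD result would be uninformative, while the protocol presents the trial as adequately sized for it.

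**Working it through.** **Inputs.** Pilot means, SDs and user counts: Background. Mean differences, intervals, alpha 0.05 two-sided, power 0.80, intracluster correlation 0.02 (range 0 to 0.1), inflation factor 1.31, drop-out 15%, 61 per group in eight homes: Sample size section.

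**1. Reproducing 0.65.** Each effect is the mean difference over the root mean square of the two SDs.
- MQS: √((14.23² + 10.58²)/2) = 12.54; 13.41/12.54 = 1.07.
- C-PAINAD: √((1.30² + 1.32²)/2) = 1.31; 0.3/1.31 = 0.229.
- Mean: (1.07 + 0.229)/2 = 0.65, as stated.

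**2. Which effect gives 38?** n per group = 2(1.96 + 0.842)²/d².
- d = 0.4: 98.1, so 99 (exact t solution 99.1).
- d = 0.65: 37.2, so 38 (exact t solution 38.1).
- Power of 38 per group at d = 0.4: about 41%.

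Carrying the numbers forward, 39 × 1.31/0.85 = 60.1, which rounds up to the stated 61 (38 gives 58.6). With 99 the result is 99 × 1.31/0.85 = 152.6, that is 153 per group or 306 in total. The 122 therefore follows from 0.65.

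**3. C-PAINAD at its pilot effect (0.229).**
- Required: 300 per group before clustering; 300 × 1.31/0.85 = 462.4, so 463 per group.
- Available: 61 × 0.85 = 51.85 completers per group; 51.85/1.31 = 39.6 effective.
- Power for one unadjusted between-group comparison: about 17% by the normal approximation, 14% with a noncentral t on 6 df (eight homes less two).
- At an intracluster correlation of 0.1: design effect 1 + (12.96 − 1) × 0.1 = 2.20; power about 12% and 10% respectively.

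**4. MQS at face value (1.07).** 14 per group would suffice. With 6 df and about 13 completers per home, planned power is 98% at a correlation of 0.02 and 86% at 0.1.

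**5. Can the MQS summary cover 30 residents?** If k of 30 are users and the rest score zero, the SD is smallest when all users have the same value: mean × √[((30 − k)/k) × (30/29)].
- Week 1, k = 5, mean 10: users average 60, SD at least 22.7. Printed: 14.23.
- Week 8, k = 7, mean 23.41: users average 100.3, SD at least 43.2. Printed: 10.58.

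The interval nevertheless matches n = 30: 1.96 × 12.54/√30 = 4.487, and 13.41 ± 4.487 = 8.923 to 17.897.

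**6. One possible reading of the MQS figures (an assumption).** Suppose the means and SDs describe users only and non-users score zero. The week 8 mean over 30 is 7 × 23.41/30 = 5.46. The week 1 mean is 5 × 10/30 = 1.67, or 7 × 10/30 = 2.33 if seven residents contributed. The change is 3.1 to 3.8 points; with SDs of about 11.2 at week 8 and 6.5 to 7.8 at week 1, d is about 0.33 to 0.42.

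**7. C-PAINAD interval.** The midpoint of −4.459 and 0.169 is −2.145, not −0.3. The formula that reproduces the MQS interval gives 1.96 × 1.31/√30 = 0.469, that is −0.769 to 0.169. The upper limit agrees; the lower does not.

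**The case against.** **The average was discarded in favour of 0.4.** That is what the text says, but step 2 shows the arithmetic did not follow. Even 0.4, properly applied, lies above the C-PAINAD pilot effect.

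**MQS may be well powered.** This stands. A reader might infer that neither outcome has adequate power, or that the MQS effect is overstated about threefold. The documents do not show that. At the printed effect, MQS power exceeds 80%. The lower value in step 6 needs the users-only assumption; a misprinted mean, SD or count would also explain the contradiction, and the pilot report is not at hand.

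**The 14 to 17% ignores the planned analysis.** Largely fair. The protocol plans four weekly baseline and twelve weekly follow-up C-PAINAD scores and a mixed model. As an illustration, assume an effect constant over 12 weeks, a common week-to-week correlation r, and an intracluster correlation unchanged by adjustment. The variance factor is (1 + 11r)/12 − 4r²/(1 + 3r): 0.169 at r = 0.3 and 0.093 at r = 0.7. With 13 completers per home and 6 df, power at 0.229 becomes about 57 to 82% (intracluster correlation 0.02) or 36 to 58% (0.1). These assumptions are favourable and not from the protocol, and most of the range is still below 80%. The stated sample size uses none of this: it is a two-group comparison of means, and t-tests are also planned.

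**The lack of a primary outcome is separate.** It does not follow from the averaging, though the averaging shows one consequence: no single outcome was chosen to size the trial. A reader might add a 14% family-wise error over three outcomes (1 − 0.95³), but that assumes independence, and the protocol expects lower pain scores as a consequence of more treatment.

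**The wrong interval limit is harmless to the sample size.** True: 0.65 reproduces from the means and SDs alone. It still needs correcting.

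**Conclusion.** The point holds in this form. The sample size rests on 0.65, an average of 1.07 and 0.23 that applies to neither outcome, and the statement that 0.4 was used is incompatible with 38 per group (99 would be needed).

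The claimed 80% is not met for C-PAINAD at its pilot effect: about 14 to 17% for a single unadjusted comparison at an intracluster correlation of 0.02. The mixed model would raise this by an amount that depends on correlations the protocol does not give. The figure also takes an uncontrolled before-after change as a stand-in for the between-group difference, as the protocol itself does.

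For MQS the power is unknown. Given the user counts and a score of zero for non-users, the printed summary cannot describe all 30 residents, so 1.07 is not a sound planning value; what should replace it cannot be determined from this document. The C-PAINAD interval has at least one wrong limit.

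**What to change.** - Drop the averaged effect, and reconcile the stated 0.4 with the 38 per group.
- Recompute the pilot MQS effect over all 30 residents with non-users scored zero, and correct the printed summary or say whom it covers.
- Correct the C-PAINAD interval.
- Restate the power of the 122 separately for MQS and C-PAINAD under the planned cluster analysis, giving the assumed intracluster and week-to-week correlations.
- Name one outcome as primary, tested at 0.05, with the other two secondary.
- Keep the MQS comparison over all residents in the randomized homes. The share medicated may be added. A comparison restricted to users should not be made, since analgesic use after randomization is what the intervention is meant to change.

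The cost is a recalculation from the pilot data plus revised wording. The downside is that the stated power becomes less favourable. The Trial status section says care homes are still being recruited, so the change can be made now.

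### The printed 38 per group does not follow from the stated effect size of 0.4; it is the answer for 0.65, so the calculation given does not support 80% power at 0.4

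*Protocol article*

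**What the plan says.** The Sample size section of the protocol article converts the pilot's pre-post changes in medication score and C-PAINAD into one effect size: "After averaging the effect sizes calculated based on these two mean differences, this was equivalent to an effect size of 0.65". It then states that "a more conservative approach of using an effect size of 0.4 was used to calculate the sample size". The operating characteristics are given as "With a significance level (α) of 0.05 and power (1-β) 0.8 for a two-sided test", and the result is that "the sample size calculation gives about 38 participants for each group". The comparison being sized is between groups; the purpose is to "evaluate a mean difference in MSQ and C-PAINAD scores between the experimental and control groups".

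Clustering and drop-out follow. The intracluster correlation is thought to lie between 0 and 0.1, and the plan chooses a value: "Due to its heterogeneous nature, we assumed an intracluster correlation of 0.02". Next, "a variance inflation factor of 1.31 will be multiplied to this calculated sample size". After a 15% drop-out allowance, "a total number of 61 participants per group is required, resulting in a total proposed sample size of 122", which is 15 to 16 residents in each of eight homes.

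**The concern.** The paragraph presents 0.4 as a deliberate margin of safety below the pilot effect. A reader will conclude that the trial has 80% power for an effect well under the one seen in the pilot. If 38 is really the requirement for 0.65, that margin was described but never applied.

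This matters most for the pain score, which carries the second objective. The pilot means and SDs in the Background give standardised changes of about 1.07 for the medication score and 0.23 for C-PAINAD. The 0.65 is their average, so it already exceeds what the pilot showed on pain. A null C-PAINAD result would be read as good evidence against an effect of 0.4 SD, when the calculation offered does not support that reading.

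**Working it through.** **Inputs (Sample size section):** two-sided alpha 0.05, power 0.80, two independent groups of equal size, effect 0.4 (stated) or 0.65 (pilot), inflation factor 1.31, drop-out 15%, 61 per group, eight homes. Four homes per arm is my assumption.

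**Step 1. Source of 0.65.**
- Medication score: 13.41 / √((14.23² + 10.58²)/2) = 1.07.
- C-PAINAD: 0.30 / √((1.30² + 1.32²)/2) = 0.23.
- Average: (1.07 + 0.23)/2 = 0.65, as printed.

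**Step 2. Size per group before inflation**, n = 2(1.960 + 0.842)²/d².

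| Effect d | Normal | t-test | Rounded up |
|---|---|---|---|
| 0.40 | 98.1 | 99.1 | 99–100 |
| 0.65 | 37.2 | 38.1 | 38–39 |

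The printed 38 matches the second row and is smaller than the first by a factor of about 2.6 (99/38). Other readings of 0.4 do not reach 38 either: a one-sided test gives 78 per group, a two-sided paired test 51–52 subjects, and Cohen's f = 0.4 about 26 per group.

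**Step 3. The inflation chain**, n × 1.31 / 0.85.
- 38: 58.6, so 59.
- 39: 60.1, so 61, the printed figure.
- 99 or 100: 152.6 or 154.1, so 153–155 per group.

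The 61 is therefore consistent with the t-test size for 0.65 rounded up to 39. It does not follow from 38 exactly.

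**Step 4. Power with 38 per group, no clustering.** At d = 0.4 the noncentrality is 0.4 × √(38/2) = 1.74, which gives 41%. At d = 0.65 power is 80–81%.

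**Step 5. Power of the planned 122 at d = 0.4, one unadjusted comparison at one time point.** After drop-out, 61 × 0.85 = 51.85 per arm, or 12.96 per home. Effective n = 51.85 / DE, and SE = √(2/effective n) in SD units.

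| ICC | Design effect (DE) | Effective n per arm | Power, normal | Power, t on 6 df |
|---|---|---|---|---|
| 0.02 | 1.31 (plan's own) | 39.6 | 43% | 32% |
| 0.02 | 1 + 11.96 × 0.02 = 1.24 | 41.8 | 45% | 34% |
| 0.10 | 1 + 11.96 × 0.10 = 2.20 | 23.6 | 28% | 21% |

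The 6 degrees of freedom are eight homes minus two arms.

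**Step 6. Effect detectable with 80% power at ICC 0.02, DE 1.24.** SE = √(2/41.8) = 0.219. The normal approximation gives 2.80 × 0.219 = 0.61 SD; the noncentral t on 6 df gives 0.74 SD. Power at 0.65 is 84% (normal) or 70% (6 df).

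**The case against.** The strongest objection is that Step 5 does not describe the whole trial. The Baseline assessment and Outcome measures sections plan 4 weekly baseline and 12 weekly follow-up measurements, and the Statistical analysis section adds a mixed-effect model that handles clustering and change from baseline. To reach 80% power at 0.4, the variance would have to fall to (0.4/0.61)² ≈ 43% of the single-measure value on the normal approximation, or (0.4/0.74)² ≈ 30% on 6 df.

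Take the mean of the 12 follow-up weeks adjusted for the 4 baselines, with ICC 0.02 and a constant week-to-week correlation between 0.1 and 0.9. The variance ratio is then 0.24–0.34, and power at 0.4 is roughly 88–97% (normal) or 74–88% (6 df). If correlation decays over time (first-order autoregressive, 0.5–0.97), power is 72–85% or 56–70%. At ICC 0.10 it stays near 40% or 30%. All these correlations are assumed, because the article gives none.

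This part of the objection stands. A reader might infer that the trial as a whole has only 34–45% power at 0.4, and the documents do not support that. It does not rescue the printed 38: the Sample size section sizes a plain difference between two groups and claims no gain from baseline or repeated measures. The same analysis section also lists Student's t-test or the Mann-Whitney test between groups, and a t-test at a single time point is the case to which the lower figures apply.

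Two smaller objections also hold in part. A reader might take the 61 as proof that 0.65 was entered. It is not proof, since it needs an unstated 39, and an unstated efficiency gain at 0.4 (for example, averaging 12 weeks at a correlation of about 0.3, or baseline adjustment at about 0.78) could also bring n near 38. And the article fixes no method for degrees of freedom, so the 6-df figures are one end of a range; the mismatch in Step 2 does not depend on them.

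**Conclusion.** The contradiction is certain: with the stated alpha, power, sidedness and comparison, 0.4 requires 99–100 per group, not 38. That 0.65 was the actual input is a strong inference from both 38 and 61, but it is not proven.

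The stated 80% power at 0.4 is therefore unsupported. On the calculation's own basis it is about half that: 41% for 38 per group, and 43–45% (normal) or 32–34% (6 df) for the planned 122 at ICC 0.02. These last figures rest on four homes per arm, equal home sizes, 15% drop-out, and one unadjusted measurement. The power of the planned mixed model at 0.4 cannot be settled from the documents. The error concerns a headline design claim and should be corrected.

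**What to change.** Keep 122 residents and correct the Sample size paragraph:

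- State that about 38 per group corresponds to an effect of 0.65, not 0.4.
- Report the effect detectable with 80% power at ICC 0.02: about 0.61 SD (normal) or 0.74 SD (6 df).
- Report the power at 0.4 for ICC 0.02 and for ICC 0.10, the top of the plan's own range.
- Label each of these figures as unadjusted and for a single time point.
- If 80% power at 0.4 is to be claimed, re-derive it from the planned mixed model with 4 baseline and 12 follow-up weeks, a stated week-to-week correlation and its source, and a stated treatment of the small number of homes.

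The cost is one reworded paragraph and a less favourable stated power. If the 0.4 claim is kept, the mixed-model calculation is extra work. No extra residents are needed.
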